## 1. Background

Body mass index (BMI, kg/m^2) is the most commonly used measure for classifying overweight and obesity. *Morbid obesity* may be defined as having a BMI above 40, or a BMI of over 35 with obesity related comorbidity (i.e. conditions that may be ameliorated or resolved after surgically induced weight loss). The prevalence of obesity is increasing in Norway. Among adults, an estimated 13.500 persons currently have a BMI of over 40.

Morbid obesity is associated with psychosocial problems, reduced work capacity, and increased morbidity and mortality from conditions such as cardiovascular disease, diabetes, and asthma. At present, bariatric surgery is the only treatment option inducing long-term weight reduction in morbidly obese patients.

Of bariatric procedures currently performed in Norway, biliopancreatic diversion with duodenal switch (duodenal switch) is perceived to be associated with the greatest degree of weight reduction, and possibly, the best quality of eating after surgery. However, both short and long-term morbidity appears to be somewhat higher than after laparoscopic Roux-en-Y gastric bypass (gastric bypass), which is the most commonly performed laparoscopic bariatric operation for morbid obesity in patients with a BMI in the range of 35 to 50.

In the gastric bypass procedure, the small bowel is arranged in such a fashion that food is diverted past the upper part of the small bowel. The length of this small bowel bypass is usually in the range of 50 to 150 cm. However, the ideal bypass length has not been determined.

Intestinal uptake of nutrients occurs chiefly after the junction of the small bowel carrying food (the alimentary limb) and the biliopancreatic limb, which transports digestive juices. This distal part of the small bowel is called the “common channel”, and its length is inversely associated with the extent of the bypass. In extremely obese patients (BMI over 50), gastric bypass performed with a short small bowel bypass provides insufficient weight reduction for a high proportion of patients. However, an extended small bowel bypass, and thus a reduced length of the common channel, is associated with increased weight reduction for this group of patients, probably with an acceptable risk of malnutrition.

The duodenal switch procedure involves the resection of  $\frac{3}{4}$  of the stomach, a small bowel bypass, and a very short common channel. This procedure has been performed as open surgery for more than 20 years, but is now feasible by laparoscopy. The procedure confers good weight reduction, and some health care providers prefer this operation in super-obese patients. Duodenal switch performed by

laparoscopy is technically more challenging than laparoscopic gastric bypass, and is possibly associated with a higher morbidity rate, in particular due to long-term complications such as exaggerated malabsorption.

It is not known whether gastric bypass or duodenal switch is the most suitable bariatric surgical technique in super-obesity, and no randomized trials have been performed to address this. Thus, we consider this research project relevant and important.

### **Feasibility of the study:**

Both gastric bypass and duodenal switch are performed at Oslo University Hospital Aker (OUH) and at Sahlgrenska University Hospital (SU) with standardized surgical techniques.

The principal investigator at SU holds a PhD in surgical treatment of morbid obesity. The registered dietician at SU involved in the study has co-authored several papers published in peer-reviewed journals on similar topics. The collaborators at OUH have not previously conducted research in the field of bariatric surgery, but have substantial general research experience. Collaborators at OUH are also currently accumulating clinical experience in this field and have participated on several international scientific congresses.

In Norway, OUH has a regional responsibility for the treatment of morbid obesity. Thus, we consider it possible to recruit a sufficient number of study participants over a short period of time. The department has the resources to carry out the practical parts of the study by personnel already employed and the financial resources for the research are available at the hospital.

## **2. Aims of the study**

To compare treatment outcome in super-obese (BMI 50-60), aged 20-50 years at inclusion, after:

- Laparoscopic gastric bypass with a long (150 cm) alimentary limb (long limb laparoscopic gastric bypass).
- Laparoscopic biliopancreatic diversion with duodenal switch (alimentary limb 200 cm and common channel 100 cm).

Primary end point: Long-term results regarding weight reduction and weight stability

Secondary end points: Long-term results regarding quality of eating and quality of life  
Per- and postoperative complications  
Postoperative mobilization and length of hospital stay  
Long-term complications (including surgical revisions)  
Changes in body composition  
Nutritional deficiencies after surgery  
Demand for hospital services (i.e. operating costs, outpatient visits)  
Long-term results regarding eating disorders  
Changes in comorbidities

Based on the same data set, more detailed studies regarding the nutritional consequences of surgery for obesity will be carried out. This is defined in more detail in a separate research protocol with the principal research fellow [name] and professor [name], Department of Medicine, Oslo University Hospital Aker.

### **Hypotheses:**

Both surgical techniques induce similar (not significantly different) weight loss and late weight regain.

The quality of life is similar in the two groups.

The quality of eating is similar in the two groups.

The incidence of perioperative and late complications are similar.

The methods are associated with similar rates of nutritional deficiencies and gastrointestinal problems.

Body composition (loss of fat and muscle mass) is changed equally in the two groups.

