### **Alternative hypotheses:**

Duodenal switch leads to a 10-20% greater weight loss (after two years) than does gastric bypass.

Weight regain from two years after surgery is greater after gastric bypass than after duodenal switch.

Duodenal switch patients experience more gastrointestinal side effects than does patients after gastric bypass.

Duodenal switch patients experience more nutritional disorders.

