### **Sample size**

Sample size calculation is based on change in weight. In a retrospective study from Sahlgrenska, mean (SD) reductions in BMI for super-obese patients 3 years after surgery were 24.9 (5.0) after duodenal switch (*n*=13) and 18.0 (6.7) after gastric bypass (*n*=19). Thus, 60 study participants would give >90% power to detect a difference in the change in BMI between groups (2-sided *t* test, *P*=.05).

Regarding quality of life, we expect that a 15% difference in score between the groups is clinically significant.

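### The primary hypothesis equates similar weight loss with a non-significant test, although only tests of difference are planned and no criterion for similarity is given

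*Protocol*

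**What the plan says.** Section 2 of the protocol, under Hypotheses, opens with the primary outcome: "Both surgical techniques induce similar (not significantly different) weight loss and late weight regain". Further statements follow without the parenthesis, among them "The quality of life is similar in the two groups" and "The incidence of perioperative and late complications are similar". Quality of eating, nutritional deficiencies and gastrointestinal problems are also called similar, and body composition is said to change equally. None of these has a margin or a criterion.

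The next heading, Alternative hypotheses, lists four directional statements. The first is "Duodenal switch leads to a 10-20% greater weight loss (after two years) than does gastric bypass"; the others concern weight regain, gastrointestinal side effects and nutritional disorders. No alternative is listed for quality of life, quality of eating, complications or body composition.

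In section 4, Statistical methods names only tests of difference: t tests, rank tests, chi-square or Fisher. Sample size sizes the trial for BMI change: "60 study participants would give >90% power to detect a difference in the change in BMI between groups" ("2-sided *t* test, *P*=.05"). It then adds, for quality of life, that "we expect that a 15% difference in score between the groups is clinically significant", but ties this to no hypothesis, SD or power.

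**The concern.** A test that fails to reject does not show that two treatments are alike. It may only show that the trial was too small for the difference that exists. A hypothesis that defines similarity as non-significance invites that mistake, and for the primary outcome the definition is in the protocol's own words.

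What is at stake is the balance of benefit and harm. The Background describes duodenal switch as technically more demanding and possibly carrying more morbidity, in exchange for greater weight loss. The trial has high power for a large weight difference and little for moderate differences in harm. If non-significance is read as similarity, the likely summary is better weight loss with similar harms, and the second half of that summary could come from lack of power alone.

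**Working it through.** **Inputs from the protocol.** BMI reductions "were 24.9 (5.0) after duodenal switch (*n*=13) and 18.0 (6.7) after gastric bypass (*n*=19"), at 3 years; total sample 60; two-sided 5% level; alternative of 10-20% greater weight loss at two years.

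**Assumptions.** 1:1 allocation, 30 per arm, no dropout (neither ratio nor dropout is stated). The 10-20% is applied to the 18.0-unit reduction after gastric bypass, giving 0.10 × 18.0 = 1.8 and 0.20 × 18.0 = 3.6 BMI units. The complication rates and quality-of-life SDs used below are not in the protocol.

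**1. The plan's own power.** The difference is 24.9 − 18.0 = 6.9.
- Root-mean-square SD = √[(5.0² + 6.7²)/2] = 5.91.
- SD pooled by the retrospective group sizes = √[(12 × 5.0² + 18 × 6.7²)/30] = 6.08.
- Standard error = SD × √(2/30) = 1.53 to 1.57.
- Power from the noncentral t distribution with 58 degrees of freedom is 99.4% (SD 5.91) and 99.1% (SD 6.08). With SD 6.7 it is 97.5%.

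The stated power of more than 90% is therefore reproduced.

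**2. Precision for BMI change.** The 95% confidence interval half-width is t(0.975; 58) × SE = 2.002 × 1.53 to 2.002 × 1.57, or about 3.1 units. An observed difference of zero would leave about ±3.1 units open. A result just short of significance would leave differences up to about 2 × 3.1, or 6.1 to 6.3 units. The planned 6.9 units would lie outside either interval if the observed SD matches the planning SD.

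**3. The protocol's own alternative.**

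| True difference (BMI units) | Power, SD 5.91 | Power, SD 6.08 | Non-significant |
|---|---|---|---|
| 1.8 (10%) | 21.3% | 20.4% | 79-80% |
| 3.6 (20%) | 64.0% | 61.6% | 36-38% |
| 6.9 (planned) | 99.4% | 99.1% | about 1% |

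**4. Complications (rates assumed).** Probability of a non-significant result with 30 per arm, by exact enumeration over both binomial distributions:

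| True rates | Chi-square, uncorrected | Fisher |
|---|---|---|
| 10% vs 20% | 81% | 90% |
| 10% vs 30% | 50% | 63% |
| 20% vs 40% | 61% | 70% |

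As an example, 3/30 against 6/30 gives Fisher P = 0.47. The 95% interval is 0.10 ± 1.96 × √(0.1 × 0.9/30 + 0.2 × 0.8/30) = 0.10 ± 0.179, that is −7.9 to +27.9 percentage points.

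**5. Quality of life (SD assumed 20 to 25 on a 0-100 scale).** The half-width is 2.002 × SD × √(2/30) = 10.3 to 12.9 points. If the protocol's 15% is read as 15 points, the interval lies inside ±15 only when the observed difference is below about 15 − 12.9 = 2.1 (SD 25) to 15 − 10.3 = 4.7 points (SD 20). A non-significant difference can be as large as the half-width itself, so non-significance is a much weaker condition than the protocol's own clinical threshold.

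**The case against.** The strongest reply is that this is an ordinary superiority design with clumsy wording. The hypotheses are followed directly by directional alternatives, so the two lists form a null and alternative pair. The tests and the sample size are consistent with that reading. This stands, and it rules out several stronger readings.

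- A reader might infer that the trial plans to declare the operations equal whenever P>.05. No section says so. The protocol supplies a definition that permits this reading, not a stated decision rule.
- A reader might infer that every hypothesis is one of similarity. The four directional alternatives contradict that. It remains true that similarity or equal change is the only stated hypothesis for quality of life, quality of eating, complications and body composition.
- A reader might carry the parenthesis over to complications and quality of life. It is attached only to weight loss and regain. The other outcomes have no criterion at all, which is a gap of a different kind.
- A reader might infer that a non-significant weight result would leave any large difference possible. It would largely exclude the planned 6.9 units; what stays open is mainly below about 6.

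It is also fair to say that the complication figures rest on assumed rates, and that Fisher alone would overstate them, since the protocol allows chi-square where appropriate. Both are shown above, and the direction is the same.

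Finally, interval reporting and rules of interpretation are often left to a statistical analysis plan, which may exist. The wording of the primary hypothesis is not: it is fixed in the protocol, and that is where the fault lies.

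**Conclusion.** The point holds in limited form. For weight loss and regain, the protocol equates similarity with non-significance. For the other outcomes it speaks of similarity or equal change with no criterion. With only tests of difference planned, a non-significant result could be misread.

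For BMI change, a true advantage of the size named in the protocol's own alternative would come out non-significant about 79-80% of the time at 1.8 units and 36-38% at 3.6 units, against about 1% at the planned 6.9 units. For complications at assumed rates of 10% and 20%, the figure is 81% to 90%, depending on the test.

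These numbers assume 30 per arm, no dropout and SDs of 5.9 to 6.1. They also assume that the 10-20% applies to the 18.0-unit figure, which is a 3-year result while the alternative refers to two years. Dropout or a larger SD would raise the proportions.

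No planned test, endpoint or sample size is invalidated. This should be fixed because it limits what the trial may conclude, but it is a fault of wording and interpretation, not of design.

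**What to change.** - Delete the parenthesis from the first hypothesis.
- Word the Hypotheses list as nulls of no difference, explicitly paired with the Alternative hypotheses.
- Report each between-group comparison as an estimate with a 95% confidence interval, and state that P>.05 will not be reported as similarity.
- For quality of life, judge the interval against the protocol's own 15% difference, stating what the 15% is a percentage of.
- For complications and nutritional deficiencies, state that 60 patients cannot establish similarity.

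A new equivalence margin for BMI change is not needed. It would add an objective that the trial did not set and is not sized for: with 30 per arm and no true difference, the chance of a 95% interval lying within ±3.6 units is only about 26-31%.

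The cost is a few lines of protocol text and intervals in the tables, with no change to design or sample size. The downside is that fewer claims of similarity can be made.

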### **Alternative hypotheses:**

Duodenal switch leads to a 10-20% greater weight loss (after two years) than does gastric bypass.

Weight regain from two years after surgery is greater after gastric bypass than after duodenal switch.

Duodenal switch patients experience more gastrointestinal side effects than does patients after gastric bypass.

Duodenal switch patients experience more nutritional disorders.

### **3. Material**

#### **Inclusion criteria:**

Patients scheduled for surgery for morbid obesity with a BMI of 50 – 60 at referral (48 – 62 at inclusion).

Age 20 to 50 years.

Signed informed consent.

#### **Exclusion criteria:**

Previous bariatric surgery.

Previous major abdominal surgery.

Other serious illnesses (such as malignancy or severe cardiopulmonary diseases).

Chronic treatment with oral steroids.

Patients with a lack of ability to cooperate in or complete the study.

### **4. Methods**

#### **Study design:**

Two-center, prospective, randomized trial.

Relevant parameters are registered prospectively in designated form (Case Record Form).

Each patient is his own control regarding the above-mentioned end points.

#### **Analytical methods:**

*Weight loss evaluated before and 1½, 6, 12, 24 and 60 months after surgery:*

Weight, BMI, and percentage weight lost.

*Body composition evaluated before and 12 and 24 months after surgery:*

Waist and hip circumferences and sagittal abdominal diameter.

Segmental bioelectrical impedance analysis in Norwegian participants. 40K spectroscopy in Swedish participants.

*Quality of life evaluated by the following questionnaires before and 12, 24 and 60 months after surgery:*

Short Form 36 health survey (SF-36).

The Obesity-related problems scale (OP-scale).

Gastrointestinal quality of life (GSRS).

Questionnaire on bowel function ("Frågeformulär tarmfunktion").

*Eating pattern (measured at similar time points):*

Three factor eating questionnaire (TFEQ).

Four-day dietary record.

Additional questions about diet and supplements.

*Health economics:*

The use of disposable surgical equipment.

Lengths of surgery and anesthesia.

Lengths of stay in post-operative department and in intensive care unit.

Length of hospital stay (expenses are converted into costs in NOK or Euros by current method applied at Sahlgrenska).

Number of visits in primary care and outpatient clinics because of obesity - before and after surgery.

*Associated diseases evaluated before and 12, 24 and 60 months after surgery:*

Diabetes: Measurement of fasting plasma glucose and insulin and record of any use of antidiabetic drugs.

Hypertension: Measurement of blood pressure and the need for medication.

Dyslipidemia: Measurement of lipids and the need for medication.

*Complications:*

Recording of early complications (within 30 days after surgery) such as anastomotic leak, hemorrhage demanding surgical intervention, pulmonary embolism, abscess, reoperations, and death etc. Further registration of late (>30-day) complications at outpatient visits.

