### **Statistical methods**

For between-group comparisons, Mann-Whitney U test and Wilcoxon's test will be used for non-parametric data, and Student's *t* test and paired *t* test for parametric analysis. Dichotomous outcome variables will be analyzed with chi-square test or Fisher's exact test as appropriate.

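### Change in fat and muscle mass is measured by a different method in each country, but the named between-arm tests have no centre or method term

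*Protocol*

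**What the plan says.** Section 2 of the protocol lists "Changes in body composition" among the secondary end points. The Hypotheses subsection then sets one statement for the whole trial, with no split by country: "Body composition (loss of fat and muscle mass) is changed equally in the two groups".

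Section 4, Analytical methods, gives the schedule ("Body composition evaluated before and 12 and 24 months after surgery") and two kinds of measurement. The first has no country split: "Waist and hip circumferences and sagittal abdominal diameter". The second does: "Segmental bioelectrical impedance analysis in Norwegian participants. 40K spectroscopy in Swedish participants". Fat and muscle mass can come only from this second kind.

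Study design describes a "Two-center, prospective, randomized trial" and adds "Each patient is his own control regarding the above-mentioned end points". It states no stratification of the allocation by centre.

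Statistical methods begins "For between-group comparisons, Mann-Whitney U test and Wilcoxon's test will be used for non-parametric data" and goes on to Student's and paired t tests, with chi-square or Fisher's exact test for dichotomous outcomes. None of these has a centre or method term. The protocol mentions neither cross-calibration of the two methods nor a separate analysis by country.

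**The concern.** The trial has one hospital in Norway and one in Sweden, so every impedance value comes from one centre and every 40K value from the other. The data cannot separate a method difference from a centre difference. The hypothesis on fat and muscle mass, read together with the list of tests, points to one two-sample comparison of change across all patients.

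If the two methods register the same true change differently, that comparison has two weaknesses. The between-method difference enters the error term and lowers power. The estimated arm difference is also a mixture of two measurement scales and is hard to interpret in kilograms.

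The direction matters because the hypothesis is one of equal change. For weight, the protocol explains similarity as the absence of a significant difference. If body composition is read the same way, extra measurement noise favours the stated hypothesis, and a real difference in fat or muscle loss could be missed.

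**Working it through.** **The plan's own figure.** The only power statement concerns BMI change (Sample size): mean reductions 24.9 (SD 5.0) and 18.0 (SD 6.7), 60 participants, two-sided 0.05, power above 90%. The difference is 24.9 − 18.0 = 6.9. The root-mean-square SD is √((5.0² + 6.7²)/2) = 5.91. With 30 per arm (1:1 assumed), the noncentral t gives 99.4%, or 97.5% with the larger SD of 6.7. The statement holds and this point does not touch it. The protocol gives no power figure for body composition.

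**What cancels.** Suppose the Swedish method reads a + s × (true value) relative to the Norwegian one. In within-patient change the constant a drops out, provided each patient keeps one method. The factor s stays.
- With true mean change μ, the centres differ in measured change by (s − 1)μ.
- With true arm difference δ, the centres estimate δ and sδ. An even pooling estimates δ(1 + s)/2, which belongs to neither scale.

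**Loss of precision.** Inputs, all assumed because the protocol does not give them: 30 per arm, an even centre split, a true effect of 0.75 within-centre SD, and a between-method difference in *measured change* of k within-centre SD. The pooled SD factor is √(1 + k²/4), and the effective sample is 1/(1 + k²/4). Power is by the noncentral t at 0.75 divided by the factor:

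| k | SD factor | Effective sample | Power |
|---|---|---|---|
| 0 | 1.000 | 100% | 81.5% |
| 0.5 | 1.031 | 94% | 79.1% |
| 1 | 1.118 | 80% | 72.4% |
| 2 | 1.414 | 50% | 52.4% |

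The even split is the worst case: with a share w of patients in one country the factor is √(1 + w(1 − w)k²). At a 2:1 split and k = 1 this is √(1 + (2/9)) = 1.106.

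**Chance imbalance.** Under simple randomisation the variance of the arm difference, in squared SD units, is (2/30)(1 + k²/4). Its centre part is (2/30)(k²/4) = k²/60, with square root 0.129k. This is the typical shift from unequal centre mix, and it is already contained in the SD factor above. As an example, 18 of 30 against 12 of 30 patients from one country shifts the estimate by (0.60 − 0.40)k = 0.2k.

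**Type I error.** By simulation with 60 patients, the unadjusted t test keeps about 5% under simple randomisation. If arms are balanced within centre it becomes conservative, at about 3% for k = 1 and about 0.5% for k = 2.

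**With a centre term.** In the same simulations, with a difference in level only, adding centre to the model holds power at about 80–82% for k from 0 to 2 (effect 0.75 SD). With an effect of 0.85 SD it stays at about 89–91% for k from 0 to 1.5.

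**The case against.** **Pooling is not stated.** The list of tests goes by data type and names no end point. A t test within each country would fit it equally well, and an analysis plan that is not shown might add a centre term. This stands as a limit: pooling is inferred from the single hypothesis and the unadjusted tests. It remains the plain reading, and the two-method design is fixed in the protocol whatever a later document adds.

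**The end point is change.** A reader might infer that any systematic difference between impedance and 40K harms the comparison. The documents do not support that. The aims and hypothesis concern change, and each patient serves as his own control, so a constant offset cancels. Only a difference in how the methods register change remains.

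**Bias.** A reader might also infer a biased comparison, with the 0.13k shift coming on top of the loss of power. It does not. Under randomisation the estimate is unbiased on average for the pooled quantity, and that shift is chance imbalance already counted in the SD factor. If allocation is balanced within centre, the shift is zero and the test is merely conservative.

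**Size and reach.** Nothing in the protocol supports a particular offset, and at 0.5 SD the loss is only about 2 points. The primary weight outcome is untouched. Waist, hip and sagittal diameter have no stated country split and already allow a comparison on a common scale.

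**Conclusion.** The point holds for change in fat and muscle mass only. Two measurements not shown to be interchangeable are fully confounded with centre, and the protocol names no analysis that separates them. If the methods register change differently, the cost is lower power and an estimate on a mixed scale.

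The size is a range, not a prediction: about 2, 9 or 29 points of power (from 82% to 79%, 72% or 52%) for differences in measured change of 0.5, 1 or 2 SD. It rests on 30 per arm, an even split and a 0.75 SD effect, all assumed. The 52% figure should not be read as the expected result, because nothing in the protocol suggests a difference as large as 2 SD. The point is worth correcting because the correction is nearly free. It does not threaten the trial's main conclusion.

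**What to change.** Add to the Statistical methods subsection that:

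- impedance and 40K changes in fat and muscle mass are compared between arms within each centre;
- the two within-centre differences are then combined, standardised within method if the scales differ, and otherwise with centre as a stratum or covariate;
- both centre-specific estimates are reported in original units;
- waist, hip and sagittal abdominal diameter serve for the common-scale comparison across the two centres.

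The condition on scale matters. A centre main effect on raw values removes a difference in level but not a difference in scale, so it is not enough if the methods stretch change differently.

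The cost is a short addition to the text and about one degree of freedom. If standardisation is used, the combined estimate is not in kilograms, which is why the centre-specific results in original units are needed beside it.

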## **5. Practical considerations and responsibilities (Norwegian part of study)**

Patients are received at the obesity clinic at the first consultation at the hospital, and examined by a physician, research nurse and nutritionist.

The treating physician will clarify whether the patient is appropriate for the study and is responsible for informing the patient about the study, inviting for participation, and for obtaining signed informed consent. This doctor obtains appropriate blood tests, and is responsible for completing all forms including preoperative data.

The nutritionist will be responsible for informing and guiding the patient by filling in the questionnaires regarding quality of life and eating patterns. All participants receive standardized information about the postoperative diet.

Data regarding health economics are obtained from medical records (length of surgery, stay in recovery and intensive care, and total hospital stay). The responsible physician fills out these forms on the participant's departure.

At outpatient visits, data registration is performed by physician and nutritionist.

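### After surgery the hospital-demand endpoint counts only visits made for obesity, so, read literally, care caused by the operation itself is not counted as resource use

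*Protocol*

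**What the plan says.** Section 2 (Aims of the study) lists among the secondary endpoints "Demand for hospital services (i.e. operating costs, outpatient visits". It sets no time limit and does not restrict visits by reason.

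Section 4 (Analytical methods, Health economics) fixes the items: disposable surgical equipment, lengths of surgery and anesthesia, time in the post-operative department and intensive care, hospital stay, and visits. The stay item reads "Length of hospital stay (expenses are converted into costs in NOK or Euros by current method applied at Sahlgrenska". The visit item reads "Number of visits in primary care and outpatient clinics because of obesity - before and after surgery".

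Section 5, which covers the Norwegian part, gives the source: "Data regarding health economics are obtained from medical records (length of surgery, stay in recovery and intensive care, and total hospital stay". It then gives the timing: "The responsible physician fills out these forms on the participant's departure".

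Late events appear elsewhere as clinical outcomes. Section 2 has the endpoint "Long-term complications (including surgical revisions", and Section 4 (Complications) provides for "Further registration of late (>30-day) complications at outpatient visits". Follow-up is 5 years (Time frame).

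**The concern.** A visit for diarrhoea, a vitamin deficiency or a surgical complication is prompted by the operation rather than by obesity. A site that applies the visit item literally would leave it out. Readmissions and revisions are not visits, and the health-economics list has no item for them after the index stay.

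The protocol expects this kind of care to differ between the arms. Section 1 says that duodenal switch "is possibly associated with a higher morbidity rate, in particular due to long-term complications such as exaggerated malabsorption". The alternative hypotheses add more gastrointestinal side effects and more nutritional disorders after that operation. At stake is whether a result labelled as hospital demand includes a component in which the authors themselves anticipate a difference. An analysis plan cannot repair this, because the gap lies in what is collected.

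**Working it through.** The protocol gives no figure for this endpoint: no late event rates, no unit costs and no expected difference. Its one design calculation, the power for change in BMI, does not bear on the point. The check is therefore a comparison of passages, followed by an illustration.

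**Step 1: endpoint against items collected**

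| Resource | Covered by the endpoint (Section 2)? | Health-economics item (Section 4)? |
|---|---|---|
| Index surgery, recovery, intensive care, stay | Yes | Yes; entered at departure in the Norwegian part |
| Visits for obesity after surgery | Yes | Yes |
| Visits for complications, nutritional or bowel problems | Yes, since visits are not restricted by reason | Not on a literal reading |
| Reoperations and revisions after discharge | Arguably, as operating costs | None named |
| Readmission days | Within the general term, but not in its explanation | None named |

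The clearest mismatch is in the third row: the aim names outpatient visits without qualification, and the methods qualify them by reason.

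**Step 2: whether the stay item could cover readmissions**

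Section 5 speaks of total hospital stay, which could in principle include later stays. A form completed when the participant leaves points to the index stay. That procedure is stated for Norway only, but Section 4, which applies to both centers, names no later inpatient item either.

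**Step 3: size of the omission**

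Let pD and pG be the proportions with a late readmission after duodenal switch and gastric bypass, and L the days per event. The omitted difference in days per patient is

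(pD − pG) × L

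All rates and durations below are assumptions.

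- Equal rates, 10% and 10%, L = 5: (0.10 − 0.10) × 5 = 0
- 20% and 10%, L = 5: (0.20 − 0.10) × 5 = 0.5 day
- 30% and 10%, L = 5: (0.30 − 0.10) × 5 = 1.0 day

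The first case matches the null hypothesis of similar late complications; the other two match the direction of the protocol's expectation. Uncounted visits would come on top and cannot be sized from the document.

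**The case against.** Several counter-arguments have force.

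- **The endpoint is narrow by its own definition.** Section 2 explains hospital demand as operating costs and outpatient visits, and Section 4 collects operating, stay and visit items. Adding readmission days therefore goes beyond that explanation. This stands for readmission days. It does not answer the restriction of visits by reason, and revision surgery is hard to keep out of operating costs.
- **The visit wording can be read broadly.** Patients attend an obesity clinic, so bariatric aftercare might be counted as obesity-related. This is a fair reading. But the term is undefined, two centers in two countries may apply it differently, and no reading of a visit count covers readmissions or revisions.
- **Late events are captured elsewhere.** Complications, revisions, nutritional deficiencies and bowel function all have their own endpoints or instruments, so the clinical differences would be reported. Bed-days could also be recovered later from medical records. Both points stand, but the protocol plans no such recovery.
- **Data entry continues after discharge.** Section 5 has data registered at outpatient visits, Section 4 (Data) speaks of continuous registration, and the case record form is not available here. It cannot be said that the form lacks these items, only that the protocol does not name them.

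A reader might go further and infer that the endpoint as a whole favours duodenal switch. The document does not support that. Section 1 calls the laparoscopic duodenal switch technically more challenging and suggests somewhat higher short-term morbidity, so the index items may count against it. A reader might also suppose that greater weight loss earns that arm fewer obesity visits; nothing in the document says so.

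**Conclusion.** The concern holds in a limited form. Read literally, the post-surgery part of the hospital-demand endpoint leaves out visits, readmissions and reoperations caused by the operation, and the protocol expects more of the underlying problems after duodenal switch. The omitted inpatient component is zero if late event rates are equal, and 0.5 to 1.0 day per patient at assumed rates of 20% to 30% versus 10% with 5 days per event. These sizes are illustrative.

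The conclusion rests on the literal reading of the visit item and on departure meaning index discharge. It concerns the omitted component only; the net direction of the full resource comparison is unknown. The endpoint is secondary, and the primary weight endpoint and its power are unaffected. The change is worth making because the data cannot be supplied at the analysis stage unless someone collects them.

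**What to change.** In Section 4 (Analytical methods, Health economics), redefine the visit item to count visits due to obesity, the operation or its complications, including nutritional and bowel problems, and exclude scheduled study visits. Add readmission days and reoperations or revisions after index discharge, up to 60 months. At both sites, take these from medical records at the visits already planned, and amend Section 5 to say so for the Norwegian part.

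If this is not wanted, restrict the endpoint's label and conclusion to index-admission resource use plus obesity-related visits.

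The cost is several added case record form items, some extra data entry at each visit, and reliance on patient report for care given elsewhere. No extra visit or test is needed.
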